#### Demographic variables.

Demographic variables will be assessed using self-report. Medical data will be obtained via self-report by the participants, and include: type of HNC, type of treatment modality and dissection type, cancer recurrences if any, comorbidities, current and previous injuries, and a list of medications.

#### Behavioural outcomes.

Social cognitive questionnaires will be informed by the Theory of Planned Behaviour [33]. Alcohol consumption and smoking status will be assessed using self-report. Exercise levels will be assessed via the Godin Leisure Time Exercise Questionnaire [34].

#### Feasibility and safety outcomes.

The feasibility and safety outcomes will be determined based on the interest rate (number of HNCS who contact us), eligibility rate (with reasons for ineligibility), recruitment rate (with reasons for refusal), 3RM testing rate (with reasons for not completing the test), HLST program adherence (including attendance, dose modifications, and progression), follow-up assessment rate (with reasons for drop out), and adverse events.

#### Health-related fitness outcomes.

3RM assessments will be used to assess upper and lower body strength with the leg press and chest press machines. RIR will be used to assess the perceived intensity of these exercises and this may be the optimal way to assess exercise intensity in terms of safety, reliability, validity, and tolerability [31]. The 3RM test is reliable and the gold standard assessment to evaluate maximal strength of resistance exercises in ‘healthy’ men and women, and it can be used by athletic trainers, health and fitness professionals and rehabilitation specialists to quantify the level of strength, to assess strength imbalances, and to evaluate training programs [31,35]. 3RM, RIR, and RPE scales are equally effective at improving muscular strength and functional performance in an older population [31], and we expect the majority of participants to be of middle to older age due to the typical age of onset of HNC.

#### Patient-reported outcomes.

Patient-reported outcomes that will be assessed include the following. QoL will be measured using the European Organization for Research and Treatment of Cancer QoL Questionnaire-C30 (EORTC QLQ-C30) [36]. Fear of cancer recurrence will be measured using the Fear of Cancer Recurrence Inventory (FCRI) [37]. Specific head and neck cancer treatment symptom burden will be assessed using the Neck Dissection Impairment Index (NDII) [38]. Self-esteem will be measured using the Rosenberg Self-Esteem Scale (RSE) [39]. Typical sleep habits will be measured using the Insomnia Severity Index (ISI) [40]. Swallowing abilities will be assessed using the MD Anderson Dysphagia Inventory [41].

#### Physical function.

Physical function assessments for participants 50 years old and up will include: 6 Minute Walk Test (6MWT), and 30 second sit to stand to assess aerobic functional capacity and lower body muscular endurance [42,43]. Active shoulder flexion and abduction ranges of motion will be measured using a goniometer to ensure ranges meet the cut points required for study eligibility outlined above. Handgrip strength will be assessed using a handgrip dynamometer [44].

#### Anthropometry and body composition.

Anthropometry and body composition will be assessed using hip to waist ratio, height, weight using a measuring tape, stadiometer, and a beam scale, respectively. Body mass index (BMI) will also be calculated and categorized based on the World Health Organization BMI classification percentiles [45]. Body composition components such as skeletal muscle mass and body fat percentage, will be estimated using a bioelectrical impedance analysis (BIA) device, the InBody770. BIA is a clinically accessible tool for estimating fat mass, lean compartments, and it also provides a measurements of phase angle. Despite its limitations, it remains valuable for assessing changes over time and has been previously utilized in patients with HNC [46–49]. Body composition will be interpreted alone and in the context of the GLIM phenotypic criteria [50].

Nutritional status will be assessed as a descriptive variable at baseline (within 1-week prior to starting the HLST program or UC period) and at post-intervention (within 1-week of completing the HLST program or UC period). Two primary tools will be used: the Global Leadership Initiative on Malnutrition (GLIM) and the Scored Patient Generated Subjective Global Assessment (PG-SGA) [50,51]. Specifically, the PG-SGA will supplement the evaluation to fulfill the criteria set by GLIM. If malnutrition is suspected, the research team will advise the study participant to seek appropriate professional care. However, this is not an exclusion criterion, and individuals suspected of having malnutrition may still participate in the study if they meet eligible criteria and wish to enroll.

### Sample size

Our goal will be to recruit 48 HNCS. With 80% power, a two-tailed alpha of p < 0.05, and adjusting for covariates that explain 25% of the variance in the outcome, we will be able to detect a standardized effect size 0.80 with 38 (19/group) evaluable HNCS allowing for a 20% loss to follow-up. We believe that this large effect on strength is realistic in our study, given that we are comparing HLST to no exercise. Additionally, all participants would not have participated in any sort of strength training within at least the past one-month. As it is difficult to power a feasibility trial on the feasibility outcomes, we have powered the trial on the first indicator of efficacy, which is muscular strength. Our study is approaching all HNCS in the Edmonton and surrounding area. Therefore, there is no viable secondary plan if the target accrual is not reached. Based on an initial review by the Alberta Cancer Registry, there are approximately 1,495 HNCS living in the Edmonton area. Based on our previous studies [13,14,20–22,25,28,52,53], we expect around 50% to be eligible and a recruitment rate of about 6%, which will allow us to reach our target.

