**Methods:**

This single-centre, two-armed, randomized controlled trial will aim to recruit 48 HNCS ≥1-year post-treatment, and randomly assign them to a 12-week Heavy Lifting Strength Training (HLST) group or Usual Care (UC) group. With 80% power, a two-tailed alpha of p < 0.05, and adjusting for covariates that explain 25% of the variance in the outcome, we will be able to detect a standardized effect size of 0.80 with 38 (19/group) evaluable HNCS, allowing for a 20% loss to follow-up. The HLST group will exercise twice weekly, progressing to lifting low repetitions of heavy loads at 80% to 100% of maximal perceived exertion, whereas the UC group will not receive any exercise prescription or instruction during the 12-week intervention. The primary efficacy outcome will be upper and lower body muscular strength assessed by 3RM tests. Secondary efficacy outcomes will include health-related fitness and patient-reported outcomes assessed with reliable physical assessments and validated questionnaires.

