### Statistical considerations

All randomized participants will be included in the analysis using an intention-to-treat approach. There will be no interim analyses. If missing data is < 10% we will conduct a complete case analysis. If missing data is > 10%, we will employ a multiple imputation missing data strategy [54,55]. Continuous variables will be described using mean (standard deviation) or median (interquartile range). Categorical variables will be described using frequencies (percentages) and confidence intervals. Descriptive analyses will be performed for participant characteristics, feasibility outcomes, adherence, and adverse events. Analysis of covariance will be performed to compare post-intervention between-group differences post-intervention in health-related fitness and patient-reported outcomes for patients with evaluable data. We will adjust for covariates such as baseline physical function levels, cancer stage, HPV status, treatments received (surgery, chemotherapy/radiotherapy, surgery + chemoradiotherapy), and time since treatment completion in the primary analysis. IBM SPSS Statistics version 28 will be used for all statistical analyses. The level of statistical significance will be set at 0.05, and all hypotheses’ tests will be two-sided.

Strategies to minimize dropouts and protocol deviations include: 1) a progression period of at least 5-weeks is in place to reach heavy loads (80% to 100% of maximal perceived exertion) in the barbell squat, bench press, and deadlift; 2) reducing the load, number of sets, and/or repetitions; 3) allowing for multiple rest days in between the two weekly exercise sessions; and 4) participants in the Usual Care Group will be offered a 4-week introduction to HLST program and/or referred to a community-based exercise program to encourage their adherence to the protocol, and to thank them for their time in the study. All participants who withdraw from the study will be invited to complete the follow-up assessments to avoid missing data for the intention-to-treat analyses.

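### The stated 80% power takes the 25% variance reduction as free; with the six or more covariate terms named for the primary ANCOVA, 38 participants give about 71–72%

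*Protocol article*

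**What the plan says.** The Sample size section of the protocol sets the target: "Our goal will be to recruit 48 HNCS". The basis is "With 80% power, a two-tailed alpha of p < 0.05". The gain from adjustment is an explicit input to the claim: "adjusting for covariates that explain 25% of the variance in the outcome, we will be able to detect a standardized effect size 0.80 with 38" evaluable participants, 19 in each arm, after an allowance of 20% for loss. The Methods part of the abstract repeats the result: "we will be able to detect a standardized effect size of 0.80 with 38 (19/group) evaluable HNCS".

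The Statistical considerations section describes the analysis as an ANCOVA of post-intervention values in patients with evaluable data. For the primary analysis it states: "We will adjust for covariates such as baseline physical function levels, cancer stage, HPV status, treatments received (surgery, chemotherapy/radiotherapy, surgery + chemoradiotherapy), and time since treatment". The test level agrees with the sample size: "The level of statistical significance will be set at 0.05, and all hypotheses’ tests will be two-sided".

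The Sample size section does not say how many covariates are meant and mentions no allowance for estimating them.

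**The concern.** Multiplying the outcome variance by (1 − R²) and then using a two-group formula treats the covariate effects as known and the covariates as exactly balanced between arms. This is harmless with one or two covariates in a large trial. It is not harmless with six or more estimated terms in 38 participants, where part of the precision gained by adjustment is spent on estimating the adjustment.

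The protocol says it is powered on muscular strength because feasibility outcomes are hard to power. If the stated power does not belong to the stated model, a non-significant strength result will be read against a power the analysis did not have. The Discussion also intends these results to inform a phase III trial.

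**Working it through.** **Inputs.** Two-sided alpha 0.05, d = 0.80, R² = 0.25, 19 per group (N = 38) and 20% loss come from Sample size; 1:1 allocation comes from Randomization and blinding. The covariates come from Statistical considerations.

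**Number of terms.** Baseline physical function 1, cancer stage 1 (I–III vs IV, as in the stratification), HPV status 1, treatment in three categories 2, time since treatment 1. The total is k = 6. The list opens with *such as*, so six is a minimum.

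**Step 1: reproduce the plan's figure.**
- n per group = 2(1.96 + 0.84)² × 0.75 / 0.80² = 18.4, rounded up to 19.
- 38 / 0.80 = 47.5, rounded up to 48.
- Power at 19 per group is 81.3% with the normal formula and 79.1% with the noncentral t on 36 df. Neither charges anything for covariates.
- Without the 25% reduction, 2(1.96 + 0.84)² / 0.80² = 24.5, so 25 per group would be needed. Power at 19 per group would be 67.0%.

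The protocol prints no formula, so its method is inferred from this match.

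**Step 2: charge for the six terms.**
- Residual df = 38 − 2 − 6 = 30. With no other cost, the noncentrality parameter is (0.80/√0.75) × √(19/2) = 2.85 and power is 78.7%. Lost degrees of freedom alone matter little.
- Expected variance inflation from chance imbalance is (N − 3)/(N − 3 − k) = 35/29 = 1.21.
- The variance relative to an unadjusted comparison becomes 0.75 × 1.21 = 0.905. The 25% reduction shrinks to about 9.5%.
- The noncentrality parameter becomes 2.85/√1.21 = 2.59. With 30 df, power is 70.8%.

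**Step 3: check by simulating the ANCOVA** (19 per group, covariates jointly explaining 25% of the variance):

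| Covariate structure | Power |
|---|---|
| Six continuous covariates | 70.8–71.5% |
| Two continuous, two binary, one three-level | 71.2% |
| The same mix, stage balanced by stratification | 71.8–72.5% |

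The prevalences used (HPV and stage about half, treatment in thirds) are assumptions. The structures differ by only 1 to 2 points.

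**Step 4: sensitivity.**
- Number of terms at R² = 0.25: one gives 77.9–78.2%, three 75–76%, five 72.4%, six about 71–72%, seven (adding sex) 69.2–69.8%, eight about 67.5%.
- R² with six terms: 0.35 gives 76.9%, 0.40 gives 80.1%, 0.50 gives 86.7%. Simulation puts the R² needed for 80% at about 0.38–0.40.
- Effect detectable with 80% power, six terms, R² = 0.25: by simulation, 0.89 SD gives 79.8% (continuous covariates) and 0.88 SD gives 80.3% (mixed covariates).
- Evaluable number with six terms: about 22–23 per group (44–46 in total, 55–58 recruited at 20% loss) restores 80%. If all 48 were evaluable, power would be 82.8–83.6%.

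**The case against.** The strongest reply is that nothing is miscalculated. The 19 per group and the 48 reproduce exactly, scaling the variance by (1 − R²) is a recognised planning approximation, and a correction for lost degrees of freedom still gives 78.7%. That is true, and it explains why standard software might not show the problem. But the larger cost is chance imbalance, and it is a real feature of the planned model at this size. Stratification removes it for only one of the six terms, and that benefit is included in the upper figures.

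Second, the covariate set may explain more than 25%, since a baseline strength measure can be a strong predictor. About 40% would be needed. The protocol names baseline physical function, not explicitly baseline 3RM, and gives no basis for a value above its own 25%. The gap is still comparable in size to the uncertainty in that planning guess.

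Third, 38 is what remains after the full 20% loss, and better retention would recover the power. This also stands, but the protocol attaches its 80% claim to 38.

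Fourth, the term count depends on coding that the article does not fix, and the final covariate list may properly be settled in an analysis plan that is not shown. The five covariates are nonetheless named for the primary analysis, and six terms is the smallest natural coding.

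Finally, feasibility is the primary aim, and the Discussion concedes that statistical significance is unlikely. This limits the consequence. It does not correct the stated power, and it sits awkwardly beside a claim of 80%.

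**Conclusion.** The concern holds. With the stated effect, variance explained, alpha and 38 evaluable participants, the primary ANCOVA with the named covariates has about 71–72% power (70.8–72.5% across methods), 8–9 points below the 80% claimed. Adjustment gains about 4–5 points over the unadjusted 67%, against the roughly 12–13 that the sample size assumes. Expressed as an effect, 80% power requires about 0.88–0.89 SD instead of 0.80.

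This rests on six terms and on 25% being the variance explained by the whole set. More terms lower the power unless they raise the explained variance. The importance is moderate: the point concerns the interpretation of a preliminary efficacy result and does not affect the feasibility aim.

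**What to change.** In the Sample size section and the abstract, state the figure for the model actually planned. With 38 evaluable participants and six covariate terms explaining 25% of the variance, power for 0.80 SD is about 71–72%; equivalently, the effect detectable with 80% power is about 0.88–0.89 SD.

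Alternatively, name a shorter list of strong predictors and recompute for that number of terms. Three terms at the same 25% give about 75–76%, so shortening the list helps but does not reach 80% unless the chosen covariates explain more, and a higher value would need justification.

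It would also help to drop the open-ended wording before the covariate list, or to point to the analysis plan where the list is fixed, so that the stated power refers to one defined model.

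The cost is a few sentences and a less favourable stated power. No additional participants or procedures are needed.

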### Feasibility and safety measures

The feasibility and safety outcomes will be determined based on the interest rate (number of HNCS who contact us), eligibility rate (with reasons for ineligibility), recruitment rate (with reasons for refusal), 3RM testing rate (with reasons for not completing the test), HLST program adherence (including attendance, dose modifications, and progression), follow-up assessment rate (with reasons for drop out), and adverse events.

The following thresholds have been adopted as indicating issues with feasibility requiring protocol modification prior to further efficacy testing: 1) Safety Concerns: > 10% of participants in the HLST group report injuries and/or adverse events likely related to the exercise intervention, which will be reported to our ethics board and the Principal Investigator ([name]) immediately; 2) Recruitment: failure to recruit 48 patients from Edmonton, Alberta which may indicate the need for a multi-centre trial moving forward; 3) Attrition Rate: > 20% of randomized participants drop out of the study; or 4) Adherence: 80% of participants adhere to the protocol.

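### Read as 6% of eligible survivors, the accrual projection gives about 45 recruits, slightly below the target of 48 and with no margin

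*Protocol article*

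**What the plan says.** The Sample size section sets the target: "Our goal will be to recruit 48 HNCS". It gives the source population, citing an initial review by the provincial cancer registry: "there are approximately 1,495 HNCS living in the Edmonton area". From these it concludes: "we expect around 50% to be eligible and a recruitment rate of about 6%, which will allow us to reach our target". The two rates are attributed to the group's previous studies.

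The same section says "Our study is approaching all HNCS in the Edmonton and surrounding area" and then that "there is no viable secondary plan if the target accrual is not reached".

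The Feasibility and safety measures section lists, among the thresholds that signal a feasibility problem calling for protocol changes before further efficacy testing, "failure to recruit 48 patients from Edmonton, Alberta which may indicate the need for a multi-centre trial moving forward".

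The power statement that leads to 48 is: "With 80% power, a two-tailed alpha of p < 0.05, and adjusting for covariates that explain 25% of the variance in the outcome", the trial can "detect a standardized effect size 0.80 with 38 (19/group) evaluable HNCS allowing for a 20% loss to follow-up".

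Table 3 lists the recruitment rate as the number and percentage randomised, without a denominator.

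**The concern.** The section offers three figures and a conclusion drawn from them. Multiplied in the obvious order (pool, then share eligible, then share recruited), they give slightly fewer than 48.

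A gap of three patients would normally pass without comment. Here the plan leaves no slack around it. The whole catchment is already being approached, no second source is available, and the recruitment threshold is set at exactly 48. Feasibility is the primary aim, so that threshold feeds the trial's main conclusion. A trial that recruited just as its authors projected would be recorded as having a recruitment problem. The target of 48 is also the smallest number that leaves 38 evaluable after 20% loss, so a shortfall passes straight through to the power statement.

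**Working it through.** **Inputs (all from Sample size, except the threshold).** Pool about 1,495; eligible around 50%; recruitment about 6%; target 48; evaluable 38 (19 per group); loss 20%; effect 0.80 SD; covariate R² 0.25; two-sided alpha 0.05; power 80%. Recruitment threshold 48 (Feasibility and safety measures).

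**Step 1: reproduce the sample size.** With residual SD √(1 − 0.25) = 0.866, the normal-approximation formula is n per group = 2 × 0.75 × (1.960 + 0.842)² / 0.80² = 18.4, rounded up to 19, so 38 in total. Allowing for loss, 38 / 0.80 = 47.5, rounded up to 48. The stated sample size reproduces.

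**Step 2: the accrual projection.** 1,495 × 0.50 = 747.5 eligible; 747.5 × 0.06 = 44.85, about 45. This is about 3 below 48.

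**Step 3: what would give 48, changing one input at a time.**
- Uptake: 48 / 747.5 = 6.42%
- Eligibility: 48 / (1,495 × 0.06) = 53.5%
- Pool: 48 / (0.50 × 0.06) = 1,600

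**Step 4: how far rounding reaches.** At 50% eligibility:

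| Uptake among eligible | Expected accrual |
|---|---|
| 5.5% | 41.1 |
| 6.0% | 44.9 |
| 6.42% | 48.0 |
| 6.5% | 48.6 |

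So 48 lies inside the range that rounds to 6%, close to its upper end. As an illustration only, taking 748 eligible, 6% uptake as exact and survivors as independent, the binomial chance of at least 48 is about 0.34. That ignores the uncertainty in both rates, so the point does not rest on it.

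**Step 5: the other denominator.** If 6% applies to all 1,495, accrual is 1,495 × 0.06 = 89.7, about 90, and the target is easily met.

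**Step 6: effect on power if 45 are randomised.** With the full 20% loss, 45 × 0.80 = 36 evaluable, 18 per group. Power at 0.80 SD with R² = 0.25:

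| Per group | Normal approximation | Noncentral t (df = 2n − 2) |
|---|---|---|
| 19 | 81.3% | 79.1% |
| 18 | 79.1% | 76.8% |

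Compared by the same method, the loss is 2.1 to 2.3 points. From 45 randomised, 38 would still be evaluable if loss were no more than 1 − 38/45 = 15.6%.

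**The case against.** The strongest reply is that the figures are openly approximate. The article qualifies the pool, the eligibility share and the recruitment rate. The 6.42% needed rounds to 6%, so the authors could hold an unrounded rate that meets the target. This stands: it turns an arithmetic failure into a projection with no margin whose central value is slightly low. It does not rescue the closing claim, which presents the point values as sufficient when they are not.

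The denominator of the 6% is also unstated. If it is everyone approached, about 90 would be recruited. That cannot be ruled out, and the eligibility share could then be a separately reported measure. It is the less natural reading, because the sentence offers both rates together as the route to the target.

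The pool may exceed 1,495, since the registry figure is for the Edmonton area while the study also approaches the surrounding area. The text does not say whether these are the same, and it counts no one beyond 1,495.

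The consequences are mild. Missing 48 is said only to be a possible sign that several centres are needed, and the Discussion already plans for that. It also concedes a low likelihood of a statistically significant effect. The lack of a fallback is disclosed and is not itself an error.

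A reader might infer two stronger things. One is that the plan's own figures predict failure of the recruitment threshold; Steps 4 and 5 show that they do not. The other is that power drops from the stated 80% to about 77%. That compares a nominal figure with a noncentral-t figure, whereas by noncentral t the 19-per-group design already has 79.1%.

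**Conclusion.** The point holds as a minor one. On the reading that 6% applies to eligible survivors and that 1,495 is the whole pool, the projection centres on about 45, some 3 below the number it is said to reach. Reaching 48 requires the upper part of the range covered by the stated rate. The article should not present this as sufficient when it has no fallback and a threshold at exactly 48, because recruitment exactly as projected would then be recorded as a feasibility issue.

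The effect on power is about 2 points, and only if the full 20% loss also occurs. The shortfall disappears if the 6% refers to all 1,495, and it shrinks or disappears if the surrounding area adds to the pool. Neither is stated.

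**What to change.** In Sample size, state the denominator of the 6% and replace the closing claim with the corrected projection. Suggested text: *At 50% eligibility and 6% uptake among eligible survivors we expect about 45 participants; reaching 48 requires about 6.4% uptake. The recruitment threshold of 48 therefore lies slightly above expected accrual.* A range such as 41 to 49 (5.5% to 6.5% uptake) would serve equally well. If the 6% refers to all 1,495, say so, give the resulting figure of about 90, and explain what the eligibility share contributes. It would also help to say whether 1,495 includes the surrounding area.

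The threshold can stay as a count of 48; turning it into a rate would be a design preference and is not needed. The cost is one or two reworded sentences and a slightly less favourable stated figure. Design, sample size and analysis are unchanged.
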